##### Level of adherence to Lycra^®^ sleeve pressure garment procedure

The level of adherence will be assessed using a conventional paper-based method (Lillo-Navarro C). The diary logbook will collect the daily amount of Lycra® sleeve pressure garment wearing period in number of hours and the reason of non-adherence if the sleeve wearing is under 3 h per day. The level of adherence will be expressed in the percentage of number of days when sleeve wearing reaches at least 3 h per day compared to the length of duration in days (start and end date of wearing period). The frequency of reasons of non-adherence will be computed as a percentage of occurred days of AEIs from the total wearing time.

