### Population

#### Patient’s eligibility

The inclusion criteria are children with ante-natal or peri-natal hemiplegic cerebral palsy, aged 5 to 10, having social insurance, written informed consent. The exclusion criteria are allergy to Lycra^®^, contra-indication to pressure therapy (e.g., skin lesions, allergic contact dermatitis), behavior or speech troubles, treatment with Botulinum Neurotoxin on the involved arm within the preceding 4 months, children under tutorship or curatorship, and predictable lack of compliance.

Patients may be discontinued from this trial at any time, firstly for voluntary discontinuation. Other specific reasons for discontinuing a patient are the administration of Botulinum Neurotoxin on the involved arm during the study and/or compliance under 80%. Any discontinuation is referred as soon as possible to the principal investigator. Data regarding the discontinued patients will be analyzed in the intention-to-treat analysis.

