##### Safety outcome

Safety outcome will be evaluated during the 6 months wearing period of PGT Lycra^®^ sleeve upper arm. Safety outcomes will include the number and intensity of adverse events of interest (AEIs). AEIs will be defined as adverse event imputable to compressive therapy and Lycra^®^ wearing, localized at the arm. AEIs will be classified into two subgroups: (i) cutaneous events linked to Lycra^®^ wearing and (ii) compression events linked to compressive therapy. According to the device classification panel from FDA regulation, the PROPENSIX PGT Lycra^®^ sleeve is a class I medical device. In this context and according to French regulations, it will not be mandatory to address a Medical Device Reporting process and a Data Safety Monitoring Board report to conduct this study. To perform this safety assessment, parents will be asked to daily report AEIs and other problems occurring during the Lycra^®^ sleeve pressure garment during wearing period on a parental self-report diary logbook. The diary logbook will be carefully checked by the investigator before the physical examination at each hospital visit (i.e., 3 months and 6 months) using a structured interview. AEIs will be classified at posteriori by the investigator using Bégaud et al. classification (minor/moderate/serious) usually used for drug clinical trial report [43]. Cutaneous events were defined as itchy contact dermatitis, red skin rash, and spots; compression events will be defined as mechanical swelling, arm pain, “Blue hand,” tingling, discomfort, sore thumb, and tightness complaint from a child. The frequency of AEIs will be computed as a percentage of occurred days of AEIs from the total wearing time.

Systolic blood pressure (SBP) and diastolic blood pressure (DBP) will also be measured as a safety outcome using an oscillometer device with a pediatric bladder.

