##### Daily activities

After enrollment, the child is asked to wear the sleeve (active or placebo) at least 3 h a day, every day, for 6 months. The sleeve has to be worn during usual daily activities, especially in activities involving bimanual performances, and during rehabilitation sessions. Each patient’s therapists (physiotherapists and occupational therapists) are informed of the child enrollment in a trial and asked to follow instructions of harmonization for rehabilitation, but there is no major modification of the usual rehabilitation care.

Written general recommendations are provided to guide rehabilitation:
Stimulation of proprioceptive function: analytic proprioception stimulation, ground bearing and weight-bearing transfers, installation quality and symmetry, mirror feedback, and dynamic proprioception stimulation (opposition and pushing games, moving of heavy objects).Stimulation of active mobility, on proximal and distal levels of the hemiplegic side, with static shoulder and arm, hand aiming, approach, and grip and release exercises.Stimulation of bimanual coordination during daily activities, developing assisting hand capacities, and passing from one hand to the other.

Additional personalized recommendations are added, regarding the child’s state of development and actual capacities of the upper extremity.

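### The formula for reasons for non-adherence repeats the adverse-event formula and cannot show any other reason; the adherence denominator has no end date for a child who stops early

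*Protocol article*

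**What the plan says.** All references are to the protocol article.

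- *Daily activities* asks for wear of "at least 3 h a day, every day, for 6 months".
- *Level of adherence to Lycra sleeve pressure garment procedure* has the diary collect daily hours and "the reason of non-adherence if the sleeve wearing is under 3 h per day". Adherence is the "percentage of number of days when sleeve wearing reaches at least 3 h per day". The denominator of this figure is worded as follows: "compared to the length of duration in days (start and end date of wearing period").
- The same section ends: "The frequency of reasons of non-adherence will be computed as a percentage of occurred days of AEIs from the total wearing time".
- *Safety outcome* says: "The frequency of AEIs will be computed as a percentage of occurred days of AEIs from the total wearing time". It restricts AEIs to events at the arm that are attributable to compression or to wearing Lycra. It also states: "Safety outcome will be evaluated during the 6 months wearing period".
- *Patient's eligibility* lists "and/or compliance under 80" per cent among the reasons for discontinuing a patient.
- *Trial design* says that the adherence level is needed for the intention-to-treat and per-protocol analyses. *Statistical analysis* defines the per-protocol exclusions by non-completion and discontinuation and gives no adherence percentage.

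**The concern.** The first problem is the reasons formula. Its numerator is AEI days, so a day missed through refusal, forgetting or a lost sleeve cannot enter it. A day with an AEI on which the sleeve was still worn for 3 h does enter it, although that day was adherent. The diary item and the summary built on it therefore measure different things, and the resulting table would duplicate the AEI table.

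The second problem is the adherence denominator. It is described by a start and an end date, and the text does not say what the end date is when a child stops before 6 months. If it is the child's last day of wear, the days after stopping drop out and the percentage does not fall when the sleeve is abandoned. If it is the end of the 6-month period, it does fall. Two analysts with the same diary could report very different figures.

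At stake is the descriptive account of how much the sleeve was worn and why it was not. The Discussion treats compliance and tolerance as a strength of the study, and *Trial design* gives the adherence level a role in the analysis.

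**Working it through.** The article states no adherence figure, so there is nothing to reproduce. The check compares definitions and then applies simple arithmetic.

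**1. Reasons formula, set side by side**

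| Item | Numerator | Denominator |
|---|---|---|
| AEI frequency (*Safety outcome*) | AEI days | total wearing time |
| Frequency of reasons (*Level of adherence*) | AEI days | total wearing time |
| What the diary collects | days under 3 h, each with a reason | – |

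The first two rows are identical. To show the effect, take an invented child with 180 days, of which 40 were under 3 h (30 refusal, 10 AEI), and 10 AEI days in all. Total wearing time is read as the 180 days.

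- Formula as written: 10/180 = 5.6%. The result stays the same whatever the other 30 reasons were.
- Days per reason over days under 3 h: refusal 30/40 = 75%; AEI 10/40 = 25%.

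**2. Adherence denominator**

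Inputs: numerator, days with at least 3 h of wear; planned course, 6 months. The article gives no day count, so 180 and 183 days are assumptions. For a child who met 3 h on every day and then stopped:

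| Stops at day | Own dates | 180 days | 183 days |
|---|---|---|---|
| 30 | 30/30 = 100% | 16.7% | 16.4% |
| 60 | 60/60 = 100% | 33.3% | 32.8% |
| 90 | 90/90 = 100% | 50.0% | 49.2% |
| 120 | 120/120 = 100% | 66.7% | 65.6% |
| 150 | 150/150 = 100% | 83.3% | 82.0% |

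The 100% is an upper limit. On own dates the score equals the share of days at 3 h or more before stopping. For a child who stops at day 90:

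| Share of days at 3 h or more before stopping | Own dates | 180 days |
|---|---|---|
| 70% | 70% | 0.70 × 90/180 = 35% |
| 80% | 80% | 0.80 × 90/180 = 40% |
| 90% | 90% | 0.90 × 90/180 = 45% |

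**3. Check at V3**

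Table 2 schedules a compliance evaluation at 3 months. A fully adherent child would then have about 90 adherent days, and 90/180 = 50% if the whole course were the denominator. A full-course denominator therefore suits only the final figure; the interim check needs days elapsed since V2.

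**The case against.** The best defence concerns the denominator. *Safety outcome*, the section just before, calls the wearing period 6 months. The sleeve is handed over at V2 and taken back at the end of the study, and the visits carry a two-week window, so start and end dates may be named only because the length varies among children who complete. On that reading, days after stopping stay in the denominator. This stands as a possible reading, so it cannot be said that the plan replaces the planned 6 months with the child's own period. What remains is that the text does not settle the matter for early stoppers.

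A reader might also infer several stronger things that the documents do not support:

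- That any child who quits early scores 100%. This needs at least 3 h on every day before stopping.
- That the per-protocol set is distorted. *Statistical analysis* excludes non-completers and discontinuations without using the percentage, so most early stoppers leave that set whatever they score.
- That 80% is an analysis threshold. It appears only as a reason for discontinuing a patient, and the article does not say that compliance there is the percentage defined under *Level of adherence*.
- That the error favours the active arm. This would need more early stopping in that arm, and no figures bear on it.

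The reasons formula is probably a wording slip. It is descriptive, it feeds no test, and the data to correct it are collected. That limits its weight, but no reading makes the sentence give the frequency of a reason other than an AEI.

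**Conclusion.** The reasons formula is wrong as written. It returns the AEI frequency and nothing else, and this conclusion rests on no assumption beyond the text.

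The adherence denominator is undefined for a child who stops early. If the last day of wear is used, such a child can score up to 100% where the share of the planned course is about 33% (stop at day 60) or about 66% (stop at day 120). These figures assume daily wear of at least 3 h before stopping and a 6-month course of 180 to 183 days. If the end of the 6-month period is used, the discrepancy vanishes.

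The consequence lies in the reported adherence level and its explanation, and in any use of this percentage for the 80% discontinuation criterion. The effect on the per-protocol set is limited, and adherence is not listed as a primary or secondary outcome. Both definitions should be corrected before analysis.

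**What to change.** 1. **Reasons.** Replace the formula with: days under 3 h with a given reason / all days under 3 h, by arm. Keep AEI days over total wearing time for the safety table only.
2. **Final adherence.** Use the days from sleeve delivery (V2) to the planned end of the 6-month period (V4) as denominator, so that days after stopping remain in it. Count the numerator over the same span. Report early stoppers and protocol-driven discontinuations separately, so that withdrawal under the protocol is not read as poor adherence.
3. **Check at V3.** Use days elapsed since V2.
4. **Reconcile** *Patient's eligibility*, *Safety outcome*, *Level of adherence* and *Statistical analysis* on what the wearing period is and which compliance measure the 80% refers to. No view is taken on that threshold.

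The cost is small: the diary already holds daily hours and reasons, so only definitions change. Reported adherence will be less favourable than with own dates as denominator.

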### Procedures

#### Intervention

##### Lycra^®^ sleeves

Lycra^®^ sleeves used in this trial are manufactured by Medical Z^®^ [44]. They are tailor-made sleeves which covers the arm from the axilla to half of the palm and the thumb, without covering other fingers (Fig. 1). The compressive dynamic Lycra^®^ sleeve, also denominated as “active Lycra^®^ sleeve,” and the placebo sleeve have the exact same appearance. No distinction between an active sleeve and a placebo sleeve can be made by investigators or patients. The active sleeve generates a homogeneous pressure ranging from 15 to 25 mmHg. The placebo sleeve provides a pressure under 5 mmHg. The sleeve notice specifies conditions of utilization: the sleeve has to be worn on the impaired arm, on bare skin, avoiding wrinkles by adjusting it from the hand to the axilla. It also provides cleaning and care precautions, as well as safety advices.

**Fig. 1 Fig1:**
[figure not shown]
A child wearing a Lycra^®^ sleeve while playing

##### Daily activities

After enrollment, the child is asked to wear the sleeve (active or placebo) at least 3 h a day, every day, for 6 months. The sleeve has to be worn during usual daily activities, especially in activities involving bimanual performances, and during rehabilitation sessions. Each patient’s therapists (physiotherapists and occupational therapists) are informed of the child enrollment in a trial and asked to follow instructions of harmonization for rehabilitation, but there is no major modification of the usual rehabilitation care.

Written general recommendations are provided to guide rehabilitation:
Stimulation of proprioceptive function: analytic proprioception stimulation, ground bearing and weight-bearing transfers, installation quality and symmetry, mirror feedback, and dynamic proprioception stimulation (opposition and pushing games, moving of heavy objects).Stimulation of active mobility, on proximal and distal levels of the hemiplegic side, with static shoulder and arm, hand aiming, approach, and grip and release exercises.Stimulation of bimanual coordination during daily activities, developing assisting hand capacities, and passing from one hand to the other.

Additional personalized recommendations are added, regarding the child’s state of development and actual capacities of the upper extremity.

#### Conduct of the trial

##### Multicenter trial

The trial takes place in 7 French pediatric rehabilitation centers. Patients are recruited in medical or medico-social structures that usually hosts children with cerebral palsy and are situated in the local areas of the involved centers. Technical and organizational support is provided by the Clinical Research Center of Lille University Hospital (Centre d’Investigation Clinique, CIC-1403_CHU-Inserm de Lille).

##### Study visits

There are 4 study visits (V1 to V4). Visit duration is 2 h for V1 and V3 and 4 h for V2 and V4. The study schedule is presented in Table 2. Flow of participants and timeline are presented in Fig. 2.

**Table 2 Tab2:** Schedule for data recording

	Inclusion visit, V1 (− 1 month)	Baseline visit, V2 (0 months*)	Control visit, V3 (3 months*)	End of study, V4 (6 months*)
Information and consent	X			
Standard examination		X	X	X
Neuro-orthopedic examination		X		X
Inclusion and exclusion criteria verification	X			
Randomization	X			
Weight, height, blood pressure, pulse	X**	X	X	X
Arm measurement	X			
AHA***		X		X
QUEST***		X		X
SEP***		X		X
PedsQL™ 3.0 CP Module		X		X
Adverse reactions report			X	X
Compliance evaluation			X	X

*AHA* Assisting Hand Assessment, *QUEST* Quality of Upper Extremity Skill Test, *PedsQL™ 3.0 CP Module* Pediatric Quality of Life Inventory 3.0 Cerebral Palsy Module

*+ 2 weeks

**Weight and height only

***Assessments without wearing the splint

**Fig. 2 Fig2:**
[figure not shown]
Experimental design. AHA, Assisting Hand Assessment

After giving their consent, participants are recruited and randomized during the inclusion visit (V1) which happens 1 month before the beginning of the intervention. The occupational therapist or investigator, specifically formed, takes precise measurements of the child’s arm, following the manufacturer’s instructions. The investigator sends the measurement data to Medical Z®, so that the confection of the sleeve can begin by the manufacturer according to randomization list (active sleeve or placebo sleeve), on condition of anonymity. The sleeve will be delivered by the manufacturer to the study center within 15 + 3 days. The investigator delivers the tailor-made sleeve (active or placebo) to the child and parents during the baseline visit (V2), with oral and written instructions regarding its utilization and care. In addition, the investigator edits the recommendations for rehabilitation harmonization, destinated to therapists involved in the child’s usual care. The sleeve is reclaimed at the end of the study. Involved therapists, investigators, patients, and their parents are blinded regarding the type of sleeve (active or placebo) received by the child according to randomization.

Outcomes evaluation occurs 1 month after inclusion, during the baseline visit (V2), and at the end of the intervention, after 6 months of daily wear of the Lycra^®^ sleeve, and during the final visit (V4). Baseline and final testing are realized without wearing the splint. AHA, the primary outcome, is assessed by a certified occupational therapist. QUEST is assessed by the same experienced occupational therapist, following the QUEST manual [35]. Neuro-orthopedic examination is conducted by the investigator following the report form of the study. SEP are recorded by an experienced neurophysiology technician. PedsQL™ 3.0 CP Module questionnaire is completed by the child’s parents. Anthropometric measurements occur at V2, V3, and V4. Compliance is monitored in a diary, specifically developed for the study purpose. Compliance data are checked at V3 and V4. Adverse reactions are recorded as well during V3 and V4.

### Data collection

All data will be recorded by trained clinical investigators and/or by the study site coordinator using an electronic case report form (eCRF Ennov EDC^®^, Ennov 33270 Floirac, France; https://ecrf.chru-lille.fr/EnnovClinical).

Data safety and security measures will be taken into account for the different study sites (restricted staff access, password protection, firewall, and virus spyware protection). To ensure the data quality, a study monitor from the trial sponsor will verify and cross-check all data against the investigator’s source document records. The essential data necessary for monitoring the primary and secondary endpoints has been identified and will be managed at regular intervals throughout the trial by the data management team of the Data Management Department of Lille University Hospital by using the predefined rules. In case of discrepancies, queries will be sent to the investigator and study site coordinator for resolution.

### Statistical analysis

The variation of the Assisting Hand Assessment (AHA) from baseline to 6 months is the primary outcome. Secondary outcomes are the Quality of Upper Extremity Skill Test (QUEST), the Pediatric Quality of Life Inventory 3.0 Cerebral Palsy module (PedsQL™ 3.0 CP Module, Parents Report), SEP parameters (N13-N20 interval, P14-N20 interval, ratios of delay conduction, amplitudes of N20-P27 and amplitude ratio), neuro-orthopedic examination (results of the second examination, 6 months later, scored in comparison with the first examination on a 0 to 3 scale: 0 = normal range of motion, 1 = lower anomaly, 2 = stable anomaly, 3 higher anomaly).

Statistical analyses will be independently performed by the Biostatistics Department of Lille University. Data will be analyzed using the SAS software (SAS Institute Inc, Cary, NC, USA), and all statistical tests will be performed with a 2-tailed alpha risk of 0.05. Baseline characteristics will be described for each group, categorical variables will be expressed as frequencies and percentages, and quantitative variables will be expressed as means and standard deviation in case of normal distribution or medians (interquartile range) otherwise normality of distributions will be assessed graphically and by using the Shapiro-Wilk test. No formal statistical comparisons of baseline characteristics will be done; clinical importance of any imbalance will be noted. For the primary analysis, both analyses (ITT and per-protocol) will be considered to support the conclusion of non-inferiority [45]. ITT population includes all randomized participants based on their original group of randomization. Per-protocol population includes all randomized patients excluding those with major protocol violations: patients who do not complete the rehabilitation procedure allocated after randomization, discontinuation for lack of compliance or personal reasons, adverse reaction. For the secondary objectives, we will use only the ITT population.

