In children with asymmetric impairments, wearing a compressive dynamic Lycra^®^ sleeve could bring a better utilization of the impaired arm, facilitate bi-manual coordination, and support learning of better motor patterns. Wearing this device while practicing bimanual activities (during school, playing, and eating activities) should result in a better improvement in bi-manual performance than practicing bi-manual activities alone. Inherent properties of Lycra^®^, such as homogenous compression, applied on the impaired upper limb of children should allow them to perform more accurate motor patterns, notably by an action on movement sensory-motor integration.

PROPENSIX study aims to evaluate efficacy of a PGT using a compressive dynamic Lycra^®^ sleeve as compared to a placebo sleeve to improve bi-manual performance measured by the Assisting Hand Assessment (AHA) in children with UCP.

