## Methods and design

Table 1 summarizes the trial registration data and information about the study design and population.

**Table 1 Tab1:** Trial registration data, design of the study, and enrollment criteria

Data category	Information
Primary registry	ClinicalTrials.gov: NCT02086214, registered on March 13, 2014
Secondary identifying numbers	ANSM ID-RCB number: 2011-A01129-32 Ethics committee: CPP 12/05
Sponsor	Lille University Hospital
Contact	Maison Régionale de la Recherche Clinique, CHU Lille, [name] [contact] Mail : [contact]
Short title	PROPENSIX study
Scientific title	PROPENSIX: Pressure Garment Therapy using compressive dynamic Lycra^®^ sleeve to improve bi-manual performance in unilateral cerebral palsy, a multicenter randomized controlled trial
Country of recruitment	France
Inclusion criteria	Unilateral cerebral palsy (perinatal or antenatal etiology), 5 to 10 years old, social insurance, written informed consent
Exclusion criteria	Allergy to Lycra^®^, contra-indication to pressure therapy (e.g., skin lesions, allergic contact dermatitis), behavior or speech troubles, Botulinum Neurotoxin received within the 4 preceding months on the impaired arm, tutorship or curatorship, predictable lack of compliance
Intervention	Treatment: Lycra^®^ sleeve (Medical Z^®^, pressure = 15 to 25 mmHg) Placebo: Placebo sleeve (Medical Z^®^, pressure < 5 mmHg)
Study type	Interventional
Study design	Prospective, randomized, placebo-controlled, parallel assignment, double-blinded, multicenter, superiority trial
Target sample size	100
Primary outcome	Performance, evaluated by AHA (Time frame: 6 months)
Secondary outcomes	Capacity, evaluated by QUEST (Time frame: 6 months) Body structures and functions, evaluated by SEP and neuro-orthopedic examination (Time frame: 6 months) Participation, evaluated by PedsQL^TM^ 3.0 CP Module (Time frame: 6 months)
Estimated primary completion date	April 2021

*AHA* Assisting Hand Assessment, *QUEST* Quality of Upper Extremity Skill Test, *PedsQL™ 3.0 CP Module*: Pediatric Quality of Life Inventory 3.0 Cerebral Palsy Module

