### Trial design

PROPENSIX is a multicenter, prospective, double-blinded, randomized, placebo-controlled superiority trial using a medical device. The seven French study centers involved are specialized in pediatric rehabilitation. Both parents/children and physicians/therapists are blinded regarding the type of sleeve (active or placebo) used during the whole duration of the trial. Un-blinding will be performed for statistical analysis since it is needed for safety outcome comparison between the groups. Primary aim statistical analysis will be also un-blinded as adherence level is mandatory for future intention-to-treat and per-protocol statistical analysis.

Enrollment into the PROPENSIX study started in December 2012 and has been completed since September 2020. The clinical phase of the study was completed in April 2021. The coding process (neurologic exams, AHA, QUEST, and quality of life tests) and data handling are ongoing until the end of 2022.

Subjects are enrolled by the investigator of each study center. The randomization is centralized. The randomization sequence was provided by an independent statistician (who did not take part in assessing the patients at any point in the study) using computer-generated random numbers structured in blocks. The block size information is not specified in the protocol to ensure that investigators are not able to anticipate treatment arm assignment. The randomization ratio is 1:1. The randomization list is maintained by the sponsor. It has been communicated to the splint manufacturer, Medical Z^®^, ensuring a randomized allocation of the sleeves to each included child, on condition of anonymity.

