### Sample size estimates

Based on the literature [26,27], the mean value of AHA was estimated at 1.8 logit (standard deviation = 2) in the placebo splint group. In the Gordon study [27], an improvement of 48% was obtained with a hand-arm bimanual intensive therapy administrated during 1 month. Based on this study and considering the duration of our therapy (6 months), we expected an improvement of 60% in favor of the Lycra® sleeve (mean AHA = 0.72 logit). Considering a two-sided Student test without adjustment, 53 patients per arm were needed (power 80%, alpha = 5%). The analysis will be adjusted for baseline AHA value, allowing to improve the design efficiency. Assuming a 0.4 correlation between the 2 measures (baseline and post-treatment) corresponding to a relative efficiency of 1.16, 45 patients were required. One hundred patients (50 in each arm) were planned to consider a 10% rate of non-analyzable data.

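### The primary analysis is worded to support non-inferiority in a placebo-controlled superiority trial that has no margin, and nothing says whether ITT or per-protocol decides

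*Protocol article*

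**What the plan says.** The design is stated consistently in four places in the protocol article.

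- **Introduction:** the aim is the efficacy of the Lycra "sleeve as compared to a placebo sleeve to improve bi-manual performance measured by the Assisting Hand Assessment (AHA) in children with UCP".
- **Table 1 (Methods and design):** "Prospective, randomized, placebo-controlled, parallel assignment, double-blinded, multicenter, superiority trial".
- **Trial design:** "multicenter, prospective, double-blinded, randomized, placebo-controlled superiority trial".
- **Sample size estimates:** a two-sided Student test with 80% power and 5% alpha, resting on the assumption that "we expected an improvement of 60% in favor of the Lycra® sleeve (mean AHA = 0.72 logit", against 1.8 logit under placebo.

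The Statistical analysis section then departs from this. For the primary analysis, it says, "both analyses (ITT and per-protocol) will be considered to support the conclusion of non-inferiority". It defines ITT as all randomised participants in their original group. It defines per-protocol by removing major violations, listed as "patients who do not complete the rehabilitation procedure allocated after randomization, discontinuation for lack of compliance or personal reasons, adverse reaction". Secondary objectives use ITT alone. The primary-outcome subsection describes only the estimation of a between-group difference in 6-month change, through the time-by-arm interaction of a cLDA model.

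**The concern.** The sentence names the conclusion that the primary analysis should support, and it names the wrong one. In a trial against a sham device, showing that the active sleeve is not much worse than placebo is no evidence of efficacy. The trial's question is whether the active sleeve is better.

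The sentence also brings in the non-inferiority habit of placing ITT and per-protocol together for the primary claim. In a superiority trial the two do not deserve equal standing. The per-protocol set is selected after randomisation, by compliance, personal reasons and adverse reactions. The sleeves differ in pressure (15 to 25 mmHg against under 5 mmHg), and the Safety outcome section lists compression events such as swelling, arm pain and tightness. Exclusions could therefore plausibly be related to arm. If ITT and per-protocol gave different answers, the plan would not say which one is the result of the trial.

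**Working it through.** **Inputs (Sample size estimates):** means 1.8 and 0.72 logit, SD 2, two-sided alpha 5%, power 80%, baseline correlation 0.4, 10% non-analysable data. The stated results are 53 per arm unadjusted, 45 per arm adjusted for baseline, and 50 per arm planned.

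**1. Reproduce the plan's own figures as a superiority calculation.**
- Difference: 1.8 − 0.72 = 1.08 logit, which is 60% of 1.8.
- Unadjusted: n = 2 × [(1.960 + 0.842) × 2 / 1.08]² = 53.8 per arm, against 53 stated (55 by the exact noncentral t).
- Baseline-adjusted: 53.8 × (1 − 0.4²) = 45.2 per arm, against 45 stated.
- Inflation: 45 / (1 − 0.10) = 50 per arm, as stated.

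The figures reproduce within 2 per arm. Every step tests against a zero difference, and no margin enters. (The stated relative efficiency of 1.16 would be 1/0.84 = 1.19 by this formula. That has no bearing here.)

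**2. What a non-inferiority conclusion would have needed.** The documents give no margin M, so a range is assumed. Take a true difference of zero, one-sided 2.5%, 80% power and adjusted SD 2 × √0.84 = 1.833. Then n per arm = 2 × [(1.960 + 0.842) × 1.833 / M]²:

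| Assumed margin (logit) | n per arm |
|---|---|
| 0.25 | 844 |
| 0.5 | 211 |
| 0.75 | 94 |
| 1.0 | 53 |
| 1.08 | 46 |

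Read the other way, 45 per arm gives SE = 1.833 × √(2/45) = 0.386. The margin that can be excluded with 80% power is 2.802 × 0.386 = 1.08 logit, which is the whole expected treatment effect. The trial was not sized for any smaller margin.

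**3. Effect on power if both analyses had to be significant.** This is a reading that the text does not state. With 45 analysable per arm:
- ITT: 1.08 / 0.386 = 2.79, so power = Φ(2.79 − 1.96) = 80%.
- Per-protocol at 80% of ITT with the same effect: 2.79 × √0.8 = 2.50, so power = Φ(2.50 − 1.96) = 71%.
- Both, with correlation √0.8 between the two statistics (bivariate normal): 68%.

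If per-protocol keeps 90% or 70% of ITT instead, joint power is 73% or 62%. The retained fractions are assumptions; the documents give none.

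**4. Which analysis decides.** Trial design mentions both ITT and per-protocol analyses without ranking them. Statistical analysis considers both for the primary outcome and restricts only the secondary objectives to ITT. Per-protocol therefore has some standing for the primary claim, and no sentence limits it.

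**The case against.** The strongest reply is that this is a drafting slip with little operational force. All tests are fixed at two-tailed 5%, the model estimates a difference, and the sample size is for superiority. With no margin and no confidence-limit rule, the plan contains no procedure by which non-inferiority could be declared. The primary-outcome subsection has a similar stray phrase, a change at 24 h in a 6-month trial, which suggests carried-over text. That is a fair explanation, but it does not correct the sentence, and swapping one word would still leave ITT and per-protocol unranked.

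Three stronger readings are tempting and should not be made.

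- **That both analyses must succeed.** The text says only that both will be considered in support of the conclusion. The power loss above is conditional on a rule that the document does not contain.
- **That an ineffective sleeve would automatically pass at any margin above about 0.77 logit.** That figure is the 95% half-width at 45 per arm (0.386 multiplied by the t quantile). It guarantees success only if the observed difference is exactly zero. With a true difference of zero, the chance of passing at that margin is about one half, and about 80% needs a margin near 1.08.
- **That the per-protocol set ignores adherence to the sleeve.** It already excludes discontinuation for lack of compliance. The eligibility section names compliance under 80% as a reason for discontinuation, and the adherence section measures hours of sleeve wear. What remains is the phrase about an allocated rehabilitation procedure. The sleeve is worn during rehabilitation sessions, so the phrase may mean the sleeve programme, but as written it does not name what was randomised.

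It also stands in the plan's favour that ITT is properly defined, that discontinued children are kept in it, and that reporting a per-protocol analysis beside it is ordinary practice.

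**Conclusion.** The point holds. The stated conclusion of the primary analysis contradicts the trial's aim, Table 1, Trial design and the sample size, and it cannot be drawn because no margin exists. The second fault is that nothing says ITT decides when the two populations disagree.

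The contradiction rests on the text alone and needs no assumption. The power figure (about 80% falling to about 68%) illustrates one possible reading. It assumes that 20% are excluded from per-protocol, that the effect is equal in both sets, and that both tests are required. The documents do not show that the sponsor intends to claim non-inferiority. The harm is that the text leaves that wording, and the choice between populations, open after the data are seen.

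**What to change.** Before unblinding, replace the sentence in Statistical analysis with:

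> The primary conclusion is superiority of the active over the placebo sleeve on 6-month change in AHA in the ITT population (two-sided alpha 5%); the per-protocol analysis is supportive only and cannot change the conclusion.

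Delete the non-inferiority reference attached to the old sentence. In the per-protocol definition, reconcile the phrase about the rehabilitation procedure allocated after randomisation with the sleeve, which is what is randomised.

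The cost is a few sentences of wording. The sample size does not change: power for the ITT superiority test is about 80% at 45 analysable per arm and 84% at 50. Timing matters because the article reports the clinical phase as completed and coding and data handling as ongoing. A correction dated after unblinding could look data-driven.
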